### Study design

This will be a pragmatic, multicenter, centrally randomized, controlled trial (Figure 1) based upon the intention-to-treat principle. To achieve allocation concealment, randomization will be carried out centrally by the coordinating study center. Independent of baseline Hb level, participants will be allocated to ESA 4000 IU/week intravenously versus 18000 IU/week intravenously of erythropoietin alfa, beta, or equivalent doses of any other commercially available agent (including darbepoetin alfa, C.E.R.A. or biosimilars and other agents, which may become available). Randomization will be stratified by enrolling center and treatments will be assigned by random permuted blocks of six patients.

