## Methods/Design

### Study population

Patients > 18 years who fulfil the following criteria:

1) Presence of anemia related to ESKD. Anemia is defined by the National Kidney Foundation as having a Hb level below 12.0 g/dL in women and 13.5 g/L in men. In the interest of a common definition for recruitment in the C.E. DOSE trial, any patient who is already receiving ESA will be eligible for randomization, as well as any patient in which the managing physician would initiate ESA treatment. Patients will be excluded if they have a Hb > 10 g/dL and are not currently receiving ESA treatment. For these individuals, ESA initiation would not be recommended based on current evidence;

2) Renal replacement therapy with hemodialysis (bicarbonate dialysis, hemofiltration, hemodiafiltration, on-line hemodiafiltration, or acetate-free biofiltration);

3) No contraindication to ESA treatment.

Patients who are already receiving treatment with any ESA may participate in the trial and will be directly enrolled and randomized into the trial without a wash-out period. This study will be conducted in agreement with the Declaration of Helsinki. Patients will provide written informed consent before commencement of the study. The following Ethics Committee approved the study: Comitato indipendente di etica medica dell'AUSL BR/1 di Brindisi, Italy.

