**Figure 1 F1:**
[figure not shown]
**Flow chart describing the selection, randomization and follow-up process of the Clinical Evaluation of the Dose of Erythropoietins (C.E. DOSE) trial**.

As there are no previous studies relating to the benefits/harms of different ESA doses for the anemia of ESKD, we established two fixed experimental doses according to the following criteria, based upon available data:

1. In the antecedent Hb target trials conducted in CKD patients [4-6], patients randomized to high (12-14 g/dL) and low (9.5-11.5 g/dL) Hb targets received between 20000 to 30000 IU/week and between 0 to 10000 g/dL IU/week of EPO, respectively.

2. In the 2004 United States Renal Data System report, 50% of hemodialysis patients incident to ESRD therapy in 1998 and followed for one year, had Hb levels between 10-13 g/dL and received more than 13000 IU/week of EPO, in particular 25% received from 13.944 to 21692 IU/week and 25% more than 21.692 IU/week of EPO [11].

Based on these assumptions the two selected experimental doses will maximize study efficacy. We will also have a safety mechanism within the trial to ensure that, after allocation to treatment, Hb values do not fall outside the safety range (of 9.5 g/dL-12.5 g/dL). A hemoglobin value above or below this range will trigger a change in the ESA dose. The prescribed ESA dose will be gradually increased or decreased by 25% until Hb values return to between 9.5 and 12.5 g/dL.

We expect recruitment to last 12 months and follow-up will be completed after 1194 cardiovascular events have occurred, which is expected to be approximately 4 years after the last patient is enrolled.

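### ESA-treated patients can be randomized with Hb already outside the trial's 9.5-12.5 g/dL safety range, so the first trial dose can move against the trial's own adjustment rule

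*Protocol article*

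**What the plan says.** Three parts of the protocol article bear on this.

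- **Study population.** For recruitment, "any patient who is already receiving ESA will be eligible for randomization", and such patients are "directly enrolled and randomized into the trial without a wash-out period". The only Hb exclusion concerns untreated patients: "Patients will be excluded if they have a Hb > 10 g/dL and are not currently receiving ESA treatment". A general criterion, "No contraindication to ESA treatment", names no Hb level.
- **Study design, allocation.** "Independent of baseline Hb level, participants will be allocated to ESA 4000 IU/week intravenously versus 18000 IU/week intravenously".
- **Study design, text after Figure 1.** After allocation, Hb is to be kept within 9.5-12.5 g/dL, which the article calls its safety range. The trigger is stated as follows: "A hemoglobin value above or below this range will trigger a change in the ESA dose". The size of each step, and when stepping stops, come next: "The prescribed ESA dose will be gradually increased or decreased by 25% until Hb values return to between 9.5 and 12.5 g/dL".

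Scheduled visits after randomization are at months 1, 2 and 3, then every 6 months.

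**The concern.** The trial has its own view of when a dose should go down or up: down above 12.5 g/dL, up below 9.5 g/dL. Entry and allocation take no account of that view for patients already on ESA. Someone whose Hb is out of range on their current dose can therefore have that dose moved the wrong way as the first act of the trial, before the safety mechanism has had a chance to work.

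What is at stake is the protection of these patients. The article excludes untreated patients above 10 g/dL because starting ESA would not be advised for them. It has no matching limit for a treated patient above 12.5 g/dL whose dose is about to rise. Comparing two doses whatever the Hb is the trial's question and is not challenged here. The point covers only patients who are outside the trial's own range at entry.

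**Working it through.** The plan prints no figure for this point, so there is none to reproduce. The check sets the rules side by side and follows the dose.

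**Inputs.** Doses of 4000 and 18000 IU/week, the range of 9.5-12.5 g/dL and the 25% steps are from Study design. Total enrolment of 2204 is from Sample size. Study design also gives example entry doses:
- 0 to 10000 IU/week in the low-target arms of the cited trials (targets 9.5-11.5 g/dL), and 20000 to 30000 in the high-target arms (12-14 g/dL);
- for a cited hemodialysis cohort, "25% received from 13.944 to 21692 IU/week and 25% more than 21.692 IU/week of EPO", where the points are read as thousands separators.

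The article gives no baseline dose or Hb for the patients to be enrolled, so these doses are illustrations only.

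**Step 1: can such a patient enter?** Yes. The anemia definition cited under Study population (below 12.0 g/dL in women, 13.5 in men) is replaced for recruitment by the common definition that admits anyone on ESA. Taken literally, it would still admit men between 12.5 and 13.5 g/dL. The contraindication criterion sets no Hb level. The cited cohort had Hb of 10-13 g/dL, a band that reaches above 12.5.

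**Step 2: high side (Hb above 12.5 g/dL, allocated to 18000).** For entry dose D, the change at allocation is 18000/D - 1. One step of the trial's rule from D would give 0.75 x D.

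| D (IU/week) | Change on moving to 18000 | 0.75 x D | 18000 / (0.75 x D) |
|---|---|---|---|
| 10000 | +80% | 7500 | 2.40 |
| 13944 | +29% | 10458 | 1.72 |
| 18000 | 0% | 13500 | 1.33 |
| 20000 | -10% | 15000 | 1.20 |
| 30000 | -40% | 22500 | 0.80 |

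The dose rises only when D is below 18000.

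**Step 3: the rule applied at once to the allocated dose.** 18000 x 0.75 = 13500. This is still an increase for any D below 13500: for D = 10000, 13500/10000 - 1 = +35%. For D = 13944 it is a small reduction, 13500/13944 - 1 = -3%.

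**Step 4: steps back to the entry dose.** Taking 25% of the current dose gives 13500, 10125, 7594. Taking 25% of the allocated dose gives 13500, 9000, 4500. Returning to 10000 or below takes 3 or 2 steps; returning to 13944 or below takes 1. The taper stops when Hb is back in range, so this is a yardstick and not the stopping rule.

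**Step 5: low side (Hb below 9.5 g/dL, allocated to 4000).** The change is 4000/D - 1, and the rule would give 1.25 x D.
- D = 10000: -60%, where the rule gives 12500.
- D = 13944: -71%, where the rule gives 17430.
- Applied at once to the allocated dose, the rule gives 4000 x 1.25 = 5000, still a cut for any D above 5000.

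**Step 6: scale.** 0.01 x 2204 = 22 patients for each 1% of entrants on one side of the range, and 22/2 = 11 in the arm that matters. This is a scaling factor, not an estimate.

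**The case against.** The strongest reply is that this is a deliberate choice in a pragmatic trial. Both strategies are defined without regard to the Hb achieved, and the range is stated to operate after allocation. A reader might infer that the protocol contradicts itself. It does not: patients are allocated, then adjusted. That part of the objection stands.

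A reader might also take the 29% and 80% increases as typical. The documents do not support that. The same part of Study design gives 20000 to 30000 IU/week for the arms targeting 12-14 g/dL, and at those doses 18000 is a reduction. A quarter of the cited cohort was above 21692 IU/week. The 10000 figure is the top of arms with low Hb targets, and two of the three cited trials enrolled patients not on dialysis. None of this rules out a patient with high Hb on a modest dose, but it leaves the frequency open.

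Nor can excess mortality be inferred. The Background evidence concerns Hb targets above 12.5 g/dL, not a single entry value, and some entry values will be transient.

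The text does not say whether a value known at randomization triggers the rule immediately. If it does, high-side entrants at 13500 or more have no net increase; those below still do. The early visits, open-label treatment and the data safety monitoring committee may limit how long a mismatch lasts, but none prevents the first dose change. Figures 1 and 2 are not shown and might add detail, but a hidden Hb limit for treated patients would conflict with the printed eligibility wording.

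Finally, an entry limit is only partial protection: a patient just inside the range can still have a large dose change. That is true, but it is the comparison the trial sets out to make, and the trial's rule calls for no adjustment there.

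**Conclusion.** The point holds as a gap in patient protection between eligibility and the safety rule, on both sides of the range. It is not an internal contradiction and does not put the trial's comparison in doubt. Following the printed text can raise the dose of a treated patient above 12.5 g/dL who enters on less than 18000 IU/week, and cut the dose of one below 9.5 g/dL who enters on more than 4000 IU/week. Immediate use of the 25% rule narrows the affected entry doses to below 13500 and above 5000 IU/week respectively, but does not close the gap.

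The conclusion rests on the eligibility text being complete as printed. How many patients are affected, and whether they would be harmed, cannot be derived from the documents. The change is worth making because it is cheap and uses the trial's own limits.

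**What to change.** Add one line to Study population, for ESA-treated patients only: Hb at or below 12.5 g/dL at randomization; patients above this remain on usual care and may be re-screened. Treat ESA-treated patients below 9.5 g/dL in the same way, deferring and re-screening them.

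Leave untreated patients under the existing rule. For them either arm starts ESA, so allocation cannot cut a dose, and those above 10 g/dL are already excluded. Leave the allocation sentence in Study design unchanged, so that allocation stays independent of Hb among eligible patients.

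The cost is that some treated candidates are deferred, which slightly slows recruitment against the planned 12 months, and the enrolled population is slightly narrower.

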**Methods/Design:**

This is a randomized, prospective open label blinded end-point (PROBE) trial due to enrol 2204 hemodialysis patients in Italy. Patients will be randomized 1:1 to 4000 IU/week versus 18000 IU/week of intravenous epoietin alfa or beta, or any other ESA in equivalent doses. The dose will be adjusted only if hemoglobin levels fall outside the 9.5-12.5 g/dL range. The primary outcome will be a composite of all-cause mortality, non fatal stroke, non fatal myocardial infarction and hospitalization for cardiovascular causes. Quality of life and costs will also be assessed.

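### One published block size of six, run separately in each centre of an open-label trial, lets a centre know up to one in four of its upcoming allocations and so weakens concealment

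*Protocol article*

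**What the plan says.** The Study design section of the protocol article states how concealment is to be secured: "To achieve allocation concealment, randomization will be carried out centrally by the coordinating study center". It then fixes the design of the list: "Randomization will be stratified by enrolling center and treatments will be assigned by random permuted blocks of six patients". Only one block length is given. The article mentions neither varying the length nor withholding it from centres.

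The abstract calls the study a "prospective open label blinded end-point (PROBE) trial" and gives the ratio and arms: "Patients will be randomized 1:1 to 4000 IU/week versus 18000 IU/week". Only outcome adjudication is blinded; each centre sees the dose assigned to each of its patients.

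The Study population section leaves some discretion at entry. Patients already on an ESA can be enrolled directly, without a wash-out. Among those not on treatment, the criterion includes "any patient in which the managing physician would initiate ESA treatment", subject to a hemoglobin limit.

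**The concern.** Concealment means that the person deciding whether and when to enrol a patient does not know the next assignment. Central randomization hides the list. It does not stop a centre from counting when three conditions hold: the centre runs its own blocks, it sees its past allocations, and it knows the block length. The article supplies all three.

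A centre that knows the next arm can choose which eligible patient to put forward, or wait. Hemodialysis centres treat a standing group of patients, many of whom could be enrolled on any of several days, so this is practicable. A selection made at that moment is built into the randomized groups. Intention-to-treat analysis keeps the groups as allocated. Blinded adjudication protects the classification of outcomes and has no bearing on who entered which arm.

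**Working it through.** The document gives no predictability figure to reproduce, so the check starts from its stated design.

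**Inputs.** Block length 6 and stratification by centre (Study design); 1:1 allocation, open label, 2204 patients (abstract). Each block therefore holds three assignments to each arm. The number of centres and their sizes are not given.

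**Certain allocations in a block of six.** There are C(6,3) = 20 equally likely orders. An allocation is certain once one arm's three places are used up.

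- Positions 1 to 3: never certain.
- Position 4: certain if the first three are all alike, 2/20 = 10%.
- Position 5: certain if the last two are alike, (4 + 4)/20 = 40%.
- Position 6: always certain, 100%.

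The sum is 0.1 + 0.4 + 1.0 = 1.5 per block, and 1.5/6 = 25%. Counting by order gives the same result: 12 orders have one certain allocation, 6 have two and 2 have three, so (12 + 12 + 6)/20 = 1.5. The general form for block length 2m is 2m/(m + 1) per block, a share of 1/(m + 1). With m = 3 this is 1/4.

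**Best guess.** Always naming the arm with more places left is right with probability 0.5, 0.6, 0.6, 0.7, 0.7 and 1.0 at positions 1 to 6. The sum is 4.1, and 4.1/6 = 68.3%, against 50% with no information.

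**Effect of centre size.** A centre that stops mid-block misses the most predictable places.

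| Patients in centre | Expected certain allocations | Share |
|---|---|---|
| 10 | 1.5 + 0.1 = 1.6 | 16% |
| 20 | 3 × 1.5 = 4.5 | 22.5% |
| 50 | 8 × 1.5 = 12 | 24% |
| complete blocks only | 1.5 per 6 | 25% |

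Across the trial, 0.25 × 2204 = 551 is therefore an upper value for the expected number, reached only if every centre completes its blocks.

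**A longer fixed block.** Fixed blocks of 8 (m = 4) would still leave 1/5 = 20% certain. Length alone does little.

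**Varied blocks.** This was a simulation with assumptions that are not in the documents: 24 patients per centre, sizes 4, 6 and 8 drawn with equal probability, and an observer who knows that set of sizes and all earlier allocations and updates by Bayes' rule.

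| Design | Certain | Best guess right |
|---|---|---|
| Fixed 6 (simulated) | 24.9% | 68.4% |
| 4, 6 or 8 at random | 2.3% | 67.2% |
| 4 or 6 at random | 5.7% | 68.7% |
| 2, 4 or 6 at random | 3.8% | 69.7% |

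The simulated fixed-six row agrees with the exact 25% and 68.3%. Varying the size among 4, 6 and 8 cuts certainty about tenfold and leaves guessing accuracy almost unchanged.

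**The case against.** Several points on the other side stand.

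- **Concealment is weakened, not abolished.** A reader might infer that the block design undoes it. The list stays hidden, the first patient of each block is a 50:50 draw, and no allocation in the first three places is ever certain.
- **25% is a ceiling on the expected share.** It needs complete blocks and staff who track every earlier assignment in their centre.
- **Overall guessing hardly improves.** If investigators act on any better-than-even guess, as in the Blackwell–Hodges model, varied blocks help little: the excess over 50% goes from about 18 to about 17 points. The gain depends on certainty being what prompts action, which is plausible but not shown.
- **Some adjustment is planned.** The Data analysis section foresees multivariable Cox models, which could partly correct measured imbalance in prognosis. They cannot reach unmeasured risk.

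A reader might also be tempted to turn this into a shift in the hazard ratio. Suppose 10–30% of certain allocations were used for steering (2.5–7.5% of 1102 patients per arm) and the steered patients carried a 1.5-fold hazard. Placing them all in the high-dose arm multiplies the hazard ratio (low versus high) by 1/1.0125 to 1/1.0375, about 0.99 to 0.96. If patients with hazard 1/1.5 were also steered to the low-dose arm, the factor would be about 0.98 to 0.94. Reversing the direction puts it above 1. The documents support none of these inputs, give no centre preferences, and do not say that centres would push the same way. No such figure should be set against the planned 0.85.

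**Conclusion.** The point holds as a modest, avoidable design weakness. With one disclosed block length per centre in an open-label 1:1 trial, a centre that counts can know up to one in four of its allocations in expectation, including the last of every block. Nothing else in the article closes that gap.

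The figure rests on three conditions: the centre knows the block length, tracks its own assignments and completes its blocks. It falls to 16% or 22.5% in centres of 10 or 20 patients. The documents do not support going further, to a claim that foreknowledge would be used, that concealment is lost altogether, or that the treatment effect would be biased by a given amount or in a given direction.

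**What to change.** Keep central randomization stratified by centre. Draw block sizes at random from several values, for example 4, 6 and 8, and hold them in a restricted document at the coordinating centre. The protocol and publications should say only that block sizes vary and are not disclosed to centres. If enrolment has begun, apply this to blocks not yet opened.

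The cost is a regenerated central list and a short amendment; sample size, event target, visits and treatment are untouched. The price is slightly looser balance in small centres: the largest possible within-centre imbalance is half the block length, so it rises from 3 patients with blocks of six to 4 when a block of eight is drawn. Certain allocations would be about 2% under the simulation's assumptions, even if centres learned the set of sizes. Some guessing would remain.

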**Figure 1 F1:**
[figure not shown]
**Flow chart describing the selection, randomization and follow-up process of the Clinical Evaluation of the Dose of Erythropoietins (C.E. DOSE) trial**.

As there are no previous studies relating to the benefits/harms of different ESA doses for the anemia of ESKD, we established two fixed experimental doses according to the following criteria, based upon available data:

1. In the antecedent Hb target trials conducted in CKD patients [4-6], patients randomized to high (12-14 g/dL) and low (9.5-11.5 g/dL) Hb targets received between 20000 to 30000 IU/week and between 0 to 10000 g/dL IU/week of EPO, respectively.

2. In the 2004 United States Renal Data System report, 50% of hemodialysis patients incident to ESRD therapy in 1998 and followed for one year, had Hb levels between 10-13 g/dL and received more than 13000 IU/week of EPO, in particular 25% received from 13.944 to 21692 IU/week and 25% more than 21.692 IU/week of EPO [11].

Based on these assumptions the two selected experimental doses will maximize study efficacy. We will also have a safety mechanism within the trial to ensure that, after allocation to treatment, Hb values do not fall outside the safety range (of 9.5 g/dL-12.5 g/dL). A hemoglobin value above or below this range will trigger a change in the ESA dose. The prescribed ESA dose will be gradually increased or decreased by 25% until Hb values return to between 9.5 and 12.5 g/dL.

We expect recruitment to last 12 months and follow-up will be completed after 1194 cardiovascular events have occurred, which is expected to be approximately 4 years after the last patient is enrolled.

During follow up, patients will receive (in a non-randomized fashion) additional co-interventions (e.g. iron, lipid lowering agents, bone disease agents, antihypertensive agents, etc.) as per their usual attending physician's practice to achieve and maintain standard dialysis clinical performance measures, relating to key CKD-related comorbidities. Non-randomized targets will include; Kt/V ≥ 1.3, serum albumin > 35 g/L, nPCR > 1.0 g/kg/day, ferrum 200-500 μg/L, transferrin saturation 30-40%, calcium 8.4-9.5 mg/dL, phosphorus 3.5-5.5 mg/dL, PTH 150-300 pg/mL, systolic pressure (predialysis) ≤ 140 mmHg, diastolic pressure (predialysis) ≤ 90 mmHg, average interdialytic weight gain for month ≤ 4% of dry weight, dialysis blood flow rate > 300 mL/min, LDL < 100 mg/dl, HDL ≥ 40 mg/dl, total cholesterol < 175 mg/dl, triglycerides < 180 mg/dl.

At the time of randomization, at months 1, 2 and 3, and at every 6 months thereafter, scheduled trial follow-up visits will be performed. The incidence of all events (outcomes) will be measured and minimum clinical workup and laboratory indicators according to standard clinical practice will be ascertained. Figure 2 shows a summary of the key practical aspects of this study.

**Figure 2 F2:**
[figure not shown]
**Summary of key practical aspects of the Clinical Evaluation of the DOSe of Erythropoietin (C.E.DOSE) trial**.

### Study Outcomes

This study will be based upon use of the Prospective Randomized Open Blinded End-Point (PROBE) technique [12]. According to the PROBE design, an independent End-Point Committee of medical specialists within the disease of interest will be established. These physicians will be unaware of allocated treatment and will review all available documents (including charts, death certificates, etc.) to provide a blinded adjudication of all outcomes. Efficacy of the two experimental interventions (fixed high dose versus fixed low dose) will be compared by reviewing the following outcomes: a) *clinical efficacy outcomes*; b) *quality of life outcomes*; c) *clinical feasibility outcomes*, and d) *costs*.

